#### Missing data

In the case of missing data, missing patterns will be assessed by comparing patient characteristics between patients with and without missing data. Appropriate data analytic techniques will be used for analysis, which may include deletion, imputation, and inclusion of an indicator of missing values.*Aim 3: To assess the sustainment of the integration of CCST into HIV programs*

### Study population

This will include healthcare providers (doctors and nurses) that provided CCST for WLHIV and healthcare administrators (medical directors) in the NISA-MIRCs study sites.

### Recruitment

Healthcare providers/administrators will be invited via letters and emails to participate in a survey and FGD.

### Data collection

Quantitative data will be collected from the healthcare providers/administrators using the Provider REport of Sustainment Scale (PRESS) [74]. The PRESS is a brief and pragmatic three-item measure of sustainment that can be used across different EBP, provider types, and settings. The PRESS captures clinic staff’s report of their clinic, team, or agency’s continued use of an EBP or innovation in practice. The PRESS has excellent psychometric characteristics. Items are measured on a 5-point Likert scale ranging from (0 [not at all] to 4 [to a very great extent]. Qualitative data regarding sustainment will be collected using FGD with doctors, nurses, and administrators in each of the sites.

### Sample size

About 36–48 health care providers (3–4 per site) will be surveyed using PRESS. We will conduct 2 FGDs (Core and Core+) with 12 participants per group.

### Data analysis

We will analyze data using a mixed-methods approach. From the quantitative data, we will classify sustainment status according to Wiltsey Stirman and colleague’s recommendations [75] and as used by Aarons and colleagues [76]. For the mixed-methods integration, we will use a QUAN+QUAL approach in which data are gathered and given equal weight [77]. We will triangulate qualitative and quantitative data to examine convergence, expansion, and complementarity when developing overall interpretations and conclusions [77–83]. We will create matrices to identify and summarize convergences and divergences in analyses of all data sources integrating results into a comprehensive picture [80]. We will first consider each type of analysis on its own terms and how they differ or converge [79, 84] by linking qualitative and quantitative databases and embedding one within the other so that each has a supportive function to play.

### Study procedures

Due to the available infrastructure in the 12 study sites, CC screening in this study will be performed using VIA. In line with the standard of care in the sites, the decision to treat preinvasive cancer lesions will be based on the result of the screening test only, and not on a histologically confirmed diagnosis (screen and treat approach). Treatment of preinvasive cancer lesions will be through ablative therapy. Participants with preinvasive lesions that are not eligible for ablative treatment, or with suspected cancer lesions, will be referred to one of the regional oncology centers of excellence (Figure 4).

**Fig. 4 Fig4:**
[figure not shown]
Algorithm for VIA-based screening, treatment, and referral

### Schedule of measurement

We will collect baseline data on the potential mechanisms (ORIC and MISII) and CC screening rates among WLHIV in the 12 facilities (Figure 5). In aim 2, each participant will be assessed at 12 months after enrollment for the receipt of CC screening (study M33). Treatment of precancerous lesions and referral of suspected cancer or lesions ineligible for treatment will be assessed at 12 and 18 months after enrollment (study M33 and M39). Posttreatment follow-up screening will be assessed at 27 and 33 months after recruitment (study M48 & M54). Data on specific potential mechanisms will be collected from the healthcare providers after recruitment and then 6 months, 12 months, and annually.

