**Methods:**

Our proposed study has formative and experimental activities across the four phases of the Exploration, Preparation, Implementation, and Sustainment (EPIS) framework. Through an implementation mapping conducted with stakeholders in the exploration phase, we identified a core package of IS (Core) and an enhanced package of IS (Core+) mostly selected from the Expert Recommendations for Implementing Change. In the preparation phase, we refined and tailored the Core and Core+ IS with the implementation resource teams for local appropriateness. In the implementation phase, we will conduct a cluster-randomized hybrid type III trial to assess the comparative effectiveness of Core versus Core+. HIV comprehensive treatment sites (*k* = 12) will be matched by region and randomized to Core or Core+ in the ratio of 1:1 stratified by region. In the sustainment phase, we will assess the sustainment of CCST at each site. The study outcomes will be assessed using RE-AIM: reach (screening rate), adoption (uptake of IS by study sites), IS fidelity (degree to which the IS occurred according to protocol), clinical intervention fidelity (delivery of CC screening, onsite treatment, and referral according to protocol), clinical effectiveness (posttreatment screen negative), and sustainment (continued integrated CCST service delivery). Additionally, we will descriptively explore potential mechanisms, including organizational readiness, implementation climate, CCST self-efficacy, and implementation intentions.

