## Methods

### Overview of study preparation and design

This is a cluster randomized trial using hybrid type III implementation-effectiveness study type [49] to assess the comparative effectiveness of a set of Core and enhanced (i.e., Core+) implementation strategies on the implementation and sustainment of cervical cancer screening and treatment for WHLIV. The hybrid type III design focuses primarily on testing IS effectiveness while observing clinical effectiveness outcomes [49]. HIV comprehensive treatment centers (*k* = 12) will be matched by region and randomized 1:1 to Core or Core+ strategies. We will assess both implementation and clinical outcomes and explore potential mechanisms that affect the study outcomes, including organizational readiness, implementation climate, CCST self-efficacy, and implementation intentions. The study is guided by two implementation science frameworks — EPIS and RE-AIM.

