#### Implementation climate measure (ICM)

The six-item ICM has three subscales that assess perceptions of the degree to which a specific evidence-based practice (EBP) or innovation is expected, supported, and rewarded (i.e., recognition) in a clinic or organization [67]. The ICM has established strong psychometric properties.

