#### Self-Efficacy/EBP Beliefs Scale

This scale assesses the perceived value of the EBP and self-efficacy regarding the ability to implement the EBP. We will use the seven items that directly assess self-efficacy and we will tailor them to refer to CCST [69]**.**

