### Data analysis

Preliminary analyses will begin with an examination of the distribution of variables to assess and describe their characteristics (means, standard deviations, quartiles, ranges, frequencies, and percentages) for overall and for Core and Core+ groups separately and to allow assessment of randomization. Randomization will be tested by performing a series of Wilcoxon rank-sum tests for continuous variables and chi-square (or Fisher’s exact) tests for categorical variables to compare the groups on baseline demographic and clinical variables. Variables on which the groups differ initially will be explored as covariates in subsequent analysis. Intent-to-treat analysis will be conducted as the primary analysis. All estimates (point estimates and 95% confidence intervals) for the study outcomes will be adjusted by the cluster effect of clinics as described below.

The screening rate (primary outcome) will be summarized by frequency and proportion. A generalized linear mixed-effect model (GLMM) [73] with a binomial link will be used to examine the difference in screening rate (reach outcome) between Core and Core+. A random intercept will be included in the model to account for the cluster effect of the site. Multivariable random effects models will be used to examine the impact of covariates on estimated intervention effects. The GLMM will be also used to compare secondary outcome measures related to adoption, implementation strategies fidelity, and clinical intervention fidelity between two intervention groups, with a binomial link for a binary outcome and a Gaussian link for a continuous outcome. The ICM, MISII, and Self-Efficacy/EBP Beliefs Scale data collected from providers will also be analyzed similarly using the GLMM.

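### Implementation climate and self-efficacy are compared between arms but have no stated measurement before the strategies start, which costs precision and any view of change

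*Protocol article*

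**What the plan says.** Four mechanisms are named. The design overview says that the study will "explore potential mechanisms that affect the study outcomes, including organizational readiness, implementation climate, CCST self-efficacy, and implementation intentions", and the abstract describes this work as descriptive: "we will descriptively explore potential mechanisms, including organizational readiness, implementation climate, CCST self-efficacy, and implementation intentions". Each has an instrument under Data collection: ORIC for readiness, ICM for climate, MISII for intentions and a self-efficacy scale. On length, the text says "The six-item ICM has three subscales that assess perceptions of the degree to which a specific evidence-based practice (EBP) or innovation is expected" for climate and "We will use the seven items that directly assess self-efficacy and we will tailor them to refer to CCST" for self-efficacy.

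The Schedule of measurement then fixes two things. At baseline: "We will collect baseline data on the potential mechanisms (ORIC and MISII) and CC screening rates among WLHIV in the 12 facilities". Later: "Data on specific potential mechanisms will be collected from the healthcare providers after recruitment and then 6 months, 12 months, and annually". The second sentence does not name its scales, and it does not place its first wave before or after the start of the strategies.

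The Aim 2 Data analysis section says: "The ICM, MISII, and Self-Efficacy/EBP Beliefs Scale data collected from providers will also be analyzed similarly using the GLMM". It follows the description of the arm comparisons, whose model is specified thus: "A random intercept will be included in the model to account for the cluster effect of the site".

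**The concern.** The baseline list and the analysis list share only one scale, MISII. ICM and self-efficacy are analysed by the model without a stated starting value.

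A mechanism is expected to move from its starting level under a strategy. With six sites per arm, and probably few providers per site, the arms can differ noticeably in climate or self-efficacy by chance before anything is implemented. A starting measurement would show that gap, allow adjustment for it, and let the trial describe movement within each arm.

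Table 2 makes the last of these important. Five of the seven strategies are given in both arms, including ongoing consultation with training and the monthly educational meetings, which are directed at the site clinical teams. The two Core+ additions are directed at people and women living with HIV. Provider climate and self-efficacy could therefore rise about equally in both arms. A contrast of Core+ with Core at follow-up would show little, and without a pre-strategy value the common rise would go unseen.

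**Working it through.** **Coverage, by the text**

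| Mechanism | Instrument | Named at baseline | In the Aim 2 model list |
|---|---|---|---|
| Readiness | ORIC | yes | no |
| Intentions | MISII | yes | yes |
| Climate | ICM (6 items) | no | yes |
| Self-efficacy | 7 items | no | yes |

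Two of the four mechanisms have a named baseline. Of the three scales in the model list, one has it.

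**Size**

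The document gives no power or precision figure for the mechanism scales. Its power figures concern reach only and do not bear on this point. The following is an illustration.

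From the document: 12 sites, k = 6 per arm (Sample size and power calculation).

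Assumed:
- m = 3–4 providers per site. The document states this figure only for the Aim 3 PRESS survey.
- ICC of the provider scores 0.1–0.3.
- Region pairing ignored.
- Correlation r = 0.5–0.7 between baseline and follow-up site means.

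*Step 1. Chance difference between arms at baseline.* In units of the provider-score SD,

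SD(difference) = √[(2/k) × (ICC + (1 − ICC)/m)].

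- ICC 0.1, m = 4: √[(2/6) × (0.1 + 0.9/4)] = √(0.3333 × 0.325) = 0.329
- ICC 0.3, m = 3: √[(2/6) × (0.3 + 0.7/3)] = √(0.3333 × 0.5333) = 0.422

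On a normal approximation, a chance gap above 0.5 score SD in either direction has probability 0.13 at the first setting and 0.24 at the second.

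*Step 2. What a baseline would buy.* Adjustment multiplies the variance of the arm contrast by 1 − r², so it removes r²: 0.25 at r = 0.5 and 0.49 at r = 0.7.

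*Step 3. Allowing for the lost degree of freedom.* The difference detectable with 80% power at two-sided 0.05 is approximately (t₀.₉₇₅ + t₀.₈₀) × SD, with 10 degrees of freedom after implementation only and 9 with a site-level baseline covariate, where SD is also multiplied by √(1 − r²).

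| Setting | Follow-up only | Adjusted, r = 0.5 | Adjusted, r = 0.7 |
|---|---|---|---|
| ICC 0.1, m = 4 | 1.02 | 0.90 | 0.74 |
| ICC 0.3, m = 3 | 1.31 | 1.15 | 0.95 |

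The detectable difference thus falls by about 12% at r = 0.5 (0.90/1.02 = 0.88) and about 27% at r = 0.7 (0.74/1.02 = 0.73), net of the degree of freedom. Even with adjustment, only large differences are detectable, so a description of change may be the more useful product.

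**The case against.** **Randomisation protects the comparison.** A reader might infer that, without a baseline, an arm difference in climate or self-efficacy cannot be distinguished from a pre-existing site difference. The document does not support that. Sites are matched by region, selected to match on type within region, and randomised within pairs, and the model carries a random intercept for site. A follow-up-only contrast is unbiased in expectation, and chance variation between sites enters its standard error. This part of the objection stands in full: validity is not at issue.

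**The scales may in fact be measured early.** A reader might also infer that ICM and self-efficacy are definitely not taken before the strategies begin. That goes too far. The later provider waves name no scales, and the first of them could be a pre-strategy measurement. The assessment schedule figure and the additional file on the instruments are not available here. Table 3 puts climate and readiness under a joint preparation and implementation heading, but that heading covers all the Aim 2 rows shown and settles nothing either way. What remains is that the text gives a closed list of two scales at baseline and leaves the timing of the other two open.

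**The aim is exploratory.** The abstract promises description, the primary outcome is reach, and no mediation claim is made. This limits the weight of the point. It does not remove the mismatch, because the Aim 2 Data analysis section goes beyond description and models these scales.

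**The magnitude is assumed.** Provider numbers are borrowed from another survey, the ICC and r are not in the document, and effective pairing would reduce the chance imbalance. All of this is correct, and the figures are only an illustration.

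**ORIC.** Its absence from the model list is a separate, minor matter. It may be intended as a starting determinant, and the present point does not rest on it.

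**Conclusion.** The point holds as a mismatch between the Schedule of measurement and the Aim 2 Data analysis section. By the text, two of the three modelled provider scales, ICM and self-efficacy, lack a stated pre-strategy measurement.

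The consequence is limited to two exploratory constructs: a less precise arm contrast, no means of seeing or adjusting for chance imbalance in them, and no measure of change in a design where both arms receive the provider-directed strategies. On the stated assumptions, the chance arm difference at baseline has an SD of about 0.33–0.42 score SD, and adjustment would remove about 25–49% of the variance of the contrast before the loss of one degree of freedom.

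It would be too strong to say that the mechanism objective fails for these constructs, or that the arm comparison is biased. Neither the primary outcome nor its analysis is affected.

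**What to change.** 1. In the Schedule of measurement, add ICM and the self-efficacy items to the ORIC and MISII baseline survey, given before the strategies start. Alternatively, if the first of the later provider waves is already that measurement, say so and name the scales taken at each wave.
2. In the Aim 2 Data analysis section, compare follow-up scores between arms adjusted for baseline, for MISII as well as for ICM and self-efficacy, and report change within each arm. Within-arm change remains descriptive, since no arm is without strategies.
3. If a pre-strategy wave is no longer possible, label ICM and self-efficacy as descriptive comparisons made after implementation only.
4. Align the abstract's descriptive wording with the planned modelling, and state what role ORIC has in the analysis.

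The cost is 6 + 7 = 13 more items in a provider survey that is already planned, and one degree of freedom for each adjusted comparison. A baseline not taken before the strategies start cannot be recovered later.

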**Fig. 5 Fig5:**
[figure not shown]
Study assessment

#### Tracking adaptations

We will use quarterly “periodic reflections” [85] with the entire investigative team to consider any ad hoc adaptations that occurred at any of the sites. We will adapt periodic reflection focus-group guides for the discussion around what adaptations may have occurred, why they occurred, at what system or organizational level, who was involved, and the time frame. We will catalog adaptations and place them within the EPIS framework identifying the phase when they occurred and whether they arose from or impacted EPIS determinants or mechanisms in outer context, inner context, bridging factors, or the innovation itself (i.e., CCST). We will also place adaptations within the FRAME-IS model for cataloging and reporting adaptations [86, 87].

#### Data handling

We will manage study data using REDCap (Research Electronic Data Capture; http://project-redcap.org/). REDCap provides user-friendly secure web-based case report forms and real-time data entry. We will use password-protected and encrypted tablets, laptops, and external drives that are institutionally certified and issued for data storage. Study data will be shared with only principal investigator-approved study staff via secure file transfer platforms.

## Discussion

In this study, we will conduct a cluster randomized, hybrid type III trial among comprehensive HIV treatment centers in Nigeria (*k* = 12) for WLHIV (*N* = 2400) to assess the comparative effectiveness of an enhanced package of IS (Core+) versus a core package of IS (Core) on the integration of CCST into HIV programs. Upon conclusion, our study will identify a set of evidence-based IS for low-income settings to integrate CCST interventions into routine HIV care to improve the health and life expectancy of WLHIV.

Meeting the WHO targets of ending CC requires countries to identify innovative implementation strategies that address contextual barriers to integration [14]. Several implementation strategies such as training of providers, community outreach, educational materials, changing service sites, task shifting, ongoing consultation, patient reminder systems, and audit-feedback mechanisms have been used in improving cervical cancer prevention in sub-Saharan Africa [41]. However, most of the studies reporting these IS did not evaluate their effectiveness or report implementation-specific outcomes [41].

To our knowledge, our study will be the first to test the effectiveness of tailored IS on the implementation of CCST among WLHIV in Nigeria. The use of hybrid type III trial design will allow our study to gather reliable evidence on implementation and clinical effectiveness outcomes. Our approach of conducting a multicenter study comprising 12 sites across the six geopolitical regions of Nigeria will ensure the representativeness of findings. Also, leveraging the PEPFAR-supported programs in Nigeria and our established partnerships will increase the likelihood of successful study implementation and service sustainment. The use of IRT as a part of the EPIS process can serve as a stakeholder engagement approach as it has been utilized in other studies [54]. We have engaged the IRT to refine and tailor the IS for local appropriateness. They will also facilitate the documentation of planned and ad hoc adaptations during the study.

Nonetheless, there are potential limitations to this study. The inadequate number of fully equipped laboratories, and the current high cost of HPV DNA tests, limits the implementation of WHO-recommended HPV screen, triage, and treat (HPV-STT) approach for WLHIV [88]. However, if the landscape changes, we will work to incorporate HPV testing instead of VIA/VILI. The 12 NISA-MIRCs sites selected for this study are secondary health facilities; thus, our findings may not be applicable to primary and tertiary healthcare facilities due to varying inner contexts.

## Conclusion

There has been a significant increase in the uptake of ART among WLHIV in Africa; however, the coverage of CCST among WLHIV who are at increased risk of CC remains low. Efforts to successfully leverage the available infrastructure for HIV care and treatment programs in low-income countries for integrated service delivery have been limited by the paucity of evidence on effective IS. With this cluster randomized, hybrid type III trial design in Nigeria, we will test and identify effective IS to integrate CCST services into routine HIV care. Results from this study could inform better implementation of CC secondary prevention intervention to improve survival among WLHIV in resource-limited settings.

## Data Availability

Not applicable.

## Abbreviations

CC: Cervical cancer
CCST: Cervical cancer screening and treatment
EPIS: Exploration, Preparation, Implementation, and Sustainment framework
IRT: Implementation resource team
IS: Implementation strategy
NISA: Nigeria Implementation Science Alliance
PEPFAR: US President’s Emergency Plan for AIDS Relief
SRC: Site research coordinators
WLHIV: Women living with HIV
